### Data and statistical analysis

All subjects who receive at least one dose of NI-03 and have baseline and post-baseline pain scores will be included in the dataset for analysis. Subjects’ data will be analyzed according to their assigned treatment (i.e., intention to treat). An additional per-protocol analysis is planned to evaluate only the data from subjects without protocol deviations (Additional file 1).

The primary efficacy variable, change in average daily worst pain score, will be analyzed using a restricted maximum likelihood (REML)-based repeated measures approach (i.e., a mixed model repeated measures (MMRM) analysis). The MMRM model will include treatment, stratification factor (oral morphine equivalent dose 0–50 mg/day versus 50–100 mg/day), center, baseline average daily pain intensity score, visit, and treatment by visit interaction as fixed-effect explanatory variables. The study center will be included in the model as a random effect. Additionally, analysis of covariance (ANCOVA) of the change from baseline to week 4 in the average daily worst pain intensity score, with the baseline score as the covariate, both treatment and stratification factor as fixed effects, and center as a random effect, will be assessed in a robustness analysis using the baseline observation carried forward (BOCF) approach.

Regular monitoring of study sites will be performed by an independent contract research organization (CRO) throughout the study period with a focus on processes for handling, reporting, and archiving data. An additional data monitoring committee will not be used for this study as the CRO will be involved with auditing study procedures and completeness of case report forms. Data sharing among study investigators will occur via secure email. The final trial dataset will be available to the Sponsor and co-authors of the study manuscript.

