### Outcomes and outcome measures

The primary outcome is change in average daily worst pain intensity score. Daily pain intensity will be scored using a numerical rating scale from 0 to 10. These values will be averaged over each week of the study, with the primary comparison between the placebo run-in period and the terminal 7 days of the treatment phase (i.e., days 22–28). Averaging pain scores over 1 week will adjust for those subjects with intermittent pain. Those with infrequent pain will be excluded if the average weekly pain score is < 4/10.

Secondary outcomes include change from baseline in least pain score, average pain score, current pain score, change in average OME and gabapentin/pregabalin daily dosages, time to first intravenous analgesic use (as rescue therapy), and change in quality of life assessed by the Pancreatic Quality of Life Instrument (PANQOLI) [26] and pain interference aspects of the brief pain inventory [27] compared to baseline. Time to first intravenous analgesic will be measured from day 1 of the trial to use of any intravenous analgesic.

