### Study recruitment and sample size justification

Study recruitment will occur at 45 centers in the USA. Various methods will be used to identify potential participants, including surveillance of clinic schedules, notification of potential referring providers, and direct advertisement to potential participants using research match tools. Trained study personnel at each site will recruit subjects.

Assuming a one-unit difference between each NI-03 dose and placebo, and a standard deviation (SD) of 1.6, the initial total sample size is calculated as 120 subjects. This will yield approximately 80% power at an overall two-sided type 1 error rate of 5% using Dunnett’s procedure. Assuming up to 5% of subjects will not qualify for the full analysis set due to incomplete data collection or failure to follow up, the total initial sample size is increased to 128 subjects. When approximately 50% of the subjects have completed the phase II study, an interim analysis will be performed to update the SD estimate primary endpoint, and the sample size will be recalculated. Data quality will also be reviewed during the interim analysis.

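### The primary MMRM's baseline covariate label omits worst pain and has no baseline-by-visit term: an ambiguity and a small, assumption-dependent precision cost at week 4

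*Protocol article*

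**What the plan says.** Under *Outcomes and outcome measures*, the Protocol article states: "The primary outcome is change in average daily worst pain intensity score". The next sentence drops the qualifier: "Daily pain intensity will be scored using a numerical rating scale from 0 to 10". These scores are averaged over each week, and the primary comparison is between the run-in and days 22–28. The same section then names other pain items: "Secondary outcomes include change from baseline in least pain score, average pain score, current pain score".

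Under *Data and statistical analysis*, the model is introduced with "The primary efficacy variable, change in average daily worst pain score, will be analyzed" by a REML-based MMRM. Its terms are treatment, opioid stratum, center and then "baseline average daily pain intensity score, visit, and treatment by visit interaction as fixed-effect explanatory variables". Treatment by visit is the only interaction listed.

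The robustness ANCOVA in the same paragraph takes as its outcome the week-4 change in "average daily worst pain intensity score, with the baseline score as the covariate". Its covariate is therefore the baseline of worst pain.

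**The concern.** Two features of the stated primary model deserve attention.

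- **The label.** The outcome is worst pain, but the covariate is described without that word, in a trial that also records average pain as an item of its own. Two analysts working from this text could fit different primary models. If average pain were used, the primary and robustness models would adjust for different baselines, and the change score would be adjusted less effectively.
- **The single slope.** Without a baseline-by-visit term, the regression of change on baseline is held equal in weeks 1 to 4. If week 4 is less correlated with baseline than week 1, the common slope is not the best one for week 4, which is where the primary contrast lies.

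Both would widen the standard error of the week-4 contrast. Neither would shift its expected value.

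**Working it through.** **What the plan supplies.** It gives no correlation between baseline and later scores, or between pain items. Its only variance input is in *Study recruitment and sample size justification*: "Assuming a one-unit difference between each NI-03 dose and placebo, and a standard deviation (SD) of 1.6". The article does not say whether that SD is raw or covariate-adjusted. There is thus no plan figure to reproduce on this point, and every correlation below is an assumption. Visits are taken as treatment weeks 1 to 4, data as complete and variances as equal (set to 1).

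**Step 1: what the label means.**
- For baseline worst pain: the outcomes section itself refers to the scores behind the primary outcome as daily pain intensity, without the qualifier, and averages them by week. In the covariate label, *average* can therefore be the weekly averaging. The ANCOVA uses the worst-pain baseline.
- For average pain: the label lacks *worst* although the outcome named in the same paragraph has it, and average pain is a separate secondary variable.

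The first reading is the more likely. The text does not exclude the second.

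**Step 2: no bias.** The adjusted week-4 contrast is (difference in mean change) − β × (difference in mean baseline). Randomization makes the expected baseline difference zero, so the choice of β or of baseline item affects variance only.

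**Step 3: cost of one slope.** Let ρ4 be the correlation of baseline with week 4. The best slope for change at week 4 is β4 = ρ4 − 1, which leaves variance 1 − ρ4². With a common slope βc the variance ratio is

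1 + (β4 − βc)² / (1 − ρ4²).

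βc comes from a simulated GLS fit with unstructured covariance and 30 per arm. Correlation between treatment weeks is assumed to fall with distance (adjacent value to the power of the lag). The last column is the square of the simulated SE ratio.

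| Baseline correlation, weeks 1–4 | Adjacent-week correlation | βc | β4 | Formula | Simulated |
|---|---|---|---|---|---|
| 0.60 throughout | 0.85 | −0.40 | −0.40 | 1.00 | 0.999² = 1.00 |
| 0.85, 0.80, 0.75, 0.70 | 0.90 | −0.191 | −0.30 | 1.02 | 1.0117² = 1.02 |
| 0.75, 0.67, 0.60, 0.50 | 0.85 | −0.317 | −0.50 | 1.04 | 1.0233² = 1.05 |
| 0.80, 0.70, 0.60, 0.50 | 0.80 | −0.284 | −0.50 | 1.06 | 1.0316² = 1.06 |
| 0.70, 0.60, 0.50, 0.40 | 0.90 | −0.340 | −0.60 | 1.08 | 1.0418² = 1.09 |
| 0.80, 0.65, 0.50, 0.40 | 0.80 | −0.284 | −0.60 | 1.12 | 1.0604² = 1.12 |

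For example, in the fourth row: (0.50 − 0.284)² / (1 − 0.25) = 0.0467 / 0.75 = 0.062. The cost is nil for a stable correlation, a few percent for moderate fading, and larger for steep fading. Across all patterns tried with fading, the variance ratio ran from 1.015 to 1.139.

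**Step 4: cost of the other item, if it were used.** Let B be baseline worst pain, Y week-4 worst pain and A baseline average pain, with corr(A, B) = r and corr(B, Y) = ρ. Assume A is related to Y only through B, so that corr(A, Y) = rρ. Then

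- Var(Y − B | A) = 2(1 − ρ) − r²(1 − ρ)²
- Var(Y − B | B) = 1 − ρ²

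At r = 0.8 and ρ = 0.6: 0.80 − 0.64 × 0.16 = 0.6976, against 0.64, a ratio of 1.09.

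| r | ρ = 0.5 | ρ = 0.7 |
|---|---|---|
| 0.7 | 1.17 | 1.09 |
| 0.8 | 1.12 | 1.06 |
| 0.9 | 1.06 | 1.03 |

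At r = 1, where the covariate is worst pain itself, the two expressions are equal and the loss is zero.

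**The case against.** The strongest reply is that the label is a one-word slip. It follows the vocabulary used for the primary outcome, the secondary item has its own name, and choosing two different baselines within one paragraph would be odd. This largely stands. A reader might infer that the plan adjusts for average pain in place of worst pain. The documents nowhere say so, and the ANCOVA points the other way. Still, exact drafting cannot be presumed: the same paragraph lists center among the fixed effects and then calls it random. The ambiguity is therefore worth closing.

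A second reply is that a common baseline slope is a legitimate, unbiased specification, and that a condensed article may leave detail to a fuller document. The first half stands. The second half stands only in part, because the article does list the model's terms down to the interaction level and this one is not among them.

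A third reply is that the losses depend on assumed correlations, and that the planned interim update of the SD, with recalculation of the sample size, could absorb a few percent of variance if the updated SD reflects the analysis model. This stands, and it is a reason to rate the point low.

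**Conclusion.** The point holds as a minor one: an ambiguous covariate label, and a stated model that imposes one baseline slope on all weeks. There is no bias under randomization.

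- **Common slope:** zero loss if the baseline correlation is stable over the four weeks, roughly 1–7% in week-4 variance if it fades moderately, and more if it fades steeply.
- **Covariate:** zero loss on the more likely reading. About 3–17% in variance if average pain were used, for r of 0.7–0.9 and ρ of 0.5–0.7.

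A reader might add the two losses and turn the sum into a number of subjects. That needs both the less likely reading of the label and a fading correlation, and the documents establish neither. Nor should the point lean on how much power the trial has for each dose. That depends on the sample-size calculation and is a separate question. Because the plan does not say what kind of SD its 1.6 is, no planned efficiency can be shown to be lost.

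**What to change.** In the MMRM description, write the covariate as *baseline (run-in) average daily worst pain intensity score*, and state that the ANCOVA uses the same baseline. Add the baseline-by-visit interaction to the MMRM fixed effects.

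The cost is a wording change and 3 model degrees of freedom (four visit-specific slopes in place of one). It is best made before unblinding, so that it cannot appear driven by the data. If a full protocol or analysis plan already specifies both, only the published description needs aligning.

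### The primary MMRM lists study center as both a fixed and a random effect; if the fixed term is fitted, roughly 2 to 13 points of power are lost, and if random-only was meant, none

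*Protocol article*

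**What the plan says.** Three statements in the article's Data and statistical analysis section concern center:

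- The fixed part of the primary MMRM has treatment and the opioid-dose stratum, and then "center, baseline average daily pain intensity score, visit, and treatment by visit interaction as fixed-effect explanatory variables".
- The next sentence, about the same model, says "The study center will be included in the model as a random effect".
- The robustness ANCOVA, with baseline carried forward, uses "both treatment and stratification factor as fixed effects, and center as a random effect".

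The section Study recruitment and sample size justification says "Study recruitment will occur at 45 centers in the USA". Its calculation reads "Assuming a one-unit difference between each NI-03 dose and placebo, and a standard deviation (SD) of 1.6", and then "the initial total sample size is calculated as 120 subjects", for about 80% power at an overall two-sided 5% level with Dunnett's procedure. This is raised to 128 for up to 5% loss. The calculation mentions no center term.

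**The concern.** The same factor cannot usefully be fixed and random in one model. The two sentences describe two different primary analyses, with different standard errors and p-values for the same data. A programmer could follow either sentence and claim to follow the plan.

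Two things are at stake. The first is prespecification: the choice could be made after results are seen. The second is precision: 45 centers need 44 fixed contrasts in a trial of about 128 subjects and four arms, and the sample size statement makes no visible allowance for them.

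**Working it through.** **Inputs from the article:** 45 centers; 120 evaluable and 128 enrolled subjects; four arms; difference 1.0; SD 1.6; Dunnett, two-sided 5%; blocks of 4 and 8 by site and opioid stratum.

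**Assumed, because the article does not state them:** equal allocation; 30% of subjects in the high-opioid stratum; even, moderately uneven or strongly uneven accrual over 45 sites; share of variance due to center (ICC) 0 or 0.05; three within-subject covariance patterns over four weekly visits.

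**Step 1. The plan's own figure.**
- With 30 per arm, SE = 1.6 × √(2/30) = 0.413, and 1/0.413 = 2.42. The Dunnett critical value is 2.38 (t) or 2.35 (normal). Power for at least one dose is 76.3% (t) or 77.5% (normal); for a given dose it is 52%.
- With 32 per arm, SE = 1.6 × √(2/32) = 0.400, and power for at least one dose is 79.0% or 80.1%.
- 120/0.95 = 126.3, so 127, rounded to 128 for four equal arms. The dropout step reproduces.

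The stated 80% is therefore slightly optimistic at 120 and is met only in the at-least-one-dose sense. The point about center does not depend on this, but there is no slack to absorb a loss.

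**Step 2. Which term governs if both are fitted.** Let Z hold the center indicators and V the within-subject covariance. The random intercept changes the covariance to V + τ²ZZ′. If the columns of Z are already in the fixed part, the treatment estimates and their variances do not depend on τ². Numerically, τ² of 0, 0.5 and 5 gave the same three treatment standard errors: 0.472, 0.461 and 0.453. The random variance is not identified, and the fixed-center model decides the result.

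**Step 3. Sparsity.** 128/45 = 2.8 and 120/45 = 2.7 subjects per center if all centers recruit. An average center cannot hold one subject per arm.

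**Step 4. Cost of the fixed term in the model the plan specifies.** Allocations were simulated. The covariance of the week-4 dose-versus-placebo contrasts was then computed with center random and with center fixed, using Dunnett critical values. Loss of power for at least one dose, in percentage points (ICC 0 / ICC 0.05):

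| N | Accrual | Compound symmetry 0.6 | Compound symmetry 0.8 | Rising variance, autoregressive 0.8 |
|---|---|---|---|---|
| 120 | even | 10.4 / 8.7 | 11.5 / 11.0 | 7.2 / 5.7 |
| 120 | moderately uneven | 8.1 / 7.5 | 10.0 / 9.1 | 6.0 / 4.6 |
| 120 | strongly uneven | 6.3 / 5.2 | 7.6 / 6.9 | 4.4 / 3.3 |
| 128 | even | 9.4 / 7.7 | 10.8 / 9.6 | 6.3 / 4.9 |
| 128 | moderately uneven | 7.7 / 6.3 | 9.1 / 7.8 | 5.2 / 4.0 |
| 128 | strongly uneven | 6.0 / 4.7 | 6.9 / 6.1 | 3.9 / 2.9 |

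At N = 120, power is 75.0 to 77.3% with center random and 63.8 to 73.9% with center fixed. At N = 128 it is 77.9 to 79.8% and 67.8 to 76.9%. Giving the fixed-center model the random model's degrees of freedom recovers at most 0.8 points, so nearly all the loss comes from larger contrast variance.

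A further simulation (N = 120, zero center variance) gave about 2 to 13 points for the week-4 MMRM contrast and 6 to 16 points for a single-time-point analysis. The range carried forward for the MMRM is 2 to 13.

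**The case against.** The best reply is that this is a drafting slip. The one sentence devoted to center makes it random, and so does the ANCOVA. On that reading the two analyses agree and no power is lost. This is the likelier intention, so the loss is conditional. It does not remove the contradiction, because the fixed-effects list says otherwise.

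A reader might infer a firm loss of 9 to 13 points. That comes from a single-time-point analysis with no true center variance, where fixed centers multiply the contrast variance by 1.22 to 1.32. The effective size per arm is then 30/1.22 = 24.6 to 30/1.32 = 22.7, and power falls from 76.3% to 67.1% or 63.5%. The plan specifies a repeated-measures model with a center main effect, and gives neither the accrual pattern nor the center variance, so the documents do not support that figure.

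A reader might also infer that centers with one subject add nothing to the treatment contrasts. That holds at a single time point. In the MMRM these subjects still inform treatment-by-visit differences through within-subject change: dropping them raised the week-4 contrast variance by about 2% (compound symmetry, 0.7) or 5% (rising variance, autoregressive).

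The sample size is also only initial, with a recalculation planned at about 50% completion. That stands, so final power is not fixed at 120 or 128. But updating the SD would not by itself repair the inefficiency of sparse fixed centers.

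**Conclusion.** The contradiction is real and visible in two adjacent sentences about the primary model. If both terms are fitted as written, the fixed-center model governs, and power to detect at least one dose at week 4 falls by roughly 2 to 13 points. That range assumes all 45 centers recruit, equal allocation, the planned difference of 1 and SD of 1.6, and the accrual, center-variance and correlation patterns listed above. If center is random only, the loss is zero.

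The documents do not support saying that the trial has lost this power, or that either specification by itself biases the comparison or inflates the type 1 error. The risk to error control comes from leaving the choice open until results are known. Because the rest of the section points to random-only, this is a should-fix rather than a fatal flaw.

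**What to change.** Delete center from the list of fixed effects in the primary MMRM and keep it as a random intercept only, matching the ANCOVA. If the sponsor does intend fixed centers, the random-effect sentence should go instead, a rule for pooling small centers should be prespecified, and the sample size should be checked against that model.

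The cost is one line of protocol or SAP wording, with no operational change. The Trial status section says phase II enrollment is ongoing, so it can be done before unblinding, and preferably before the interim sample size recalculation.

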### Patient safety and adverse event recording

Safety will be monitored through weekly contact: telephone calls during weeks 1 and 3 and office visits during weeks 2 and 4. All adverse events will be recorded. The investigator will determine both the severity of the event and relationship to study treatment, based on clinical judgment. Subjects may discontinue treatment if adverse events occur or they may be removed from treatment as determined by the investigator. Rationale for drug discontinuation will be reported. The investigator will not be un-blinded if a serious adverse event occurs. Every serious adverse event (death, life-threatening event, hospitalization, persistent disability, or other important medical event) will be reported to the lead investigator as soon as possible to determine causality. The event will be submitted expeditiously in the event of an adverse drug reaction. Medical care for study-related adverse events will be paid for by the study Sponsor.

## Discussion

This phase I/II study will assess the safety and efficacy of NI-03 for the treatment of CP-associated pain in a double-blind, randomized, placebo-controlled trial. During the phase I study, a pharmacokinetic evaluation will occur after one dose, with safety assessments at 1 week. The subsequent phase II study will consist of a 1-week, single-blind, run-in period followed by a 4-week, double-blind treatment period to compare the change in average daily worst pain intensity scores. Key secondary outcomes will include changes in concurrent analgesic dose and quality of life scores. The purpose of this study is to fill an important clinical gap in providing an effective medical treatment option for CP-associated pain.

The management of painful CP begins with abstinence from alcohol and tobacco and often includes assessment for local complications or pancreatic duct obstruction, which may lead to procedural or surgical interventions. Analgesia is commonly provided in keeping with the World Health Organization pain ladder for those in whom anatomic intervention is not clearly warranted. Unfortunately, these interventions involve generic management of chronic pain and do not target the underlying mechanisms leading to CP-associated pain or CP-related disease progression.

Oral analgesic agents, including antioxidants and pregabalin, addressing the mechanisms of painful CP have been previously studied [3–7]. However, antioxidants have not been consistently shown to improve pain scores in patients with CP [3–6]. Pregabalin has demonstrated improvement in a small trial, but its use was limited due to side effects [7]. Serine protease inhibitors, including an oral agent called camostat mesilate or NI-03 have been approved for use in Japan to treat painful CP [8]. However, the original studies were conducted primarily on male patients of Asian descent during the late 1970s, and their results may not be applicable to an American demographic including women and other ethnicities. Furthermore, the original studies did not evaluate safety or efficacy of doses other than 200 mg three times daily. Therefore, a modern study including an evaluation of the pharmacokinetics of varying doses is required. Additionally, subjects need to be randomized to varying doses to determine the optimal dose for safety and efficacy.

Pain remains a common and frequently debilitating symptom for many patients with CP. Despite the associated morbidity, high-quality evidence-based treatment options remain limited. This study will evaluate the pharmacokinetics, safety, and efficacy of an orally available serine protease inhibitor, NI-03, for CP-associated pain. If efficacious, this will be a novel agent for treatment of symptoms among patients with CP in the USA.

